## Methods

### Study Design and Setting

The study is a 24-week, parallel-group, randomized trial for DVA clients (ADF veterans and their dependents) who have been cleared by their treating EP or physiotherapist as able to safely transition to self-managed PA. EP or physiotherapist practices that we engage to recruit eligible participants will be randomly assigned to the Active Choices or comparison program, using an allocation ratio of 1:1.

Randomization will be performed using a simple randomization procedure, based on a computer-generated sequence. Allocation of practices will be concealed at the time of assignment, and members of the research team who will analyze the study data will be blinded to allocation. However, blinding of participants and those who will administer the interventions and outcome assessments will not be possible due to the nature of the program.

Data will be collected from participants at 3 timepoints: baseline, end-intervention (Week 12), and follow-up (Week 24). The trial will be conducted in Brisbane, Australia. Intervention delivery and data collection will take place at the allied health practice the participant attends. A flow chart of the trial is shown in Figure 1.

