#### Comparison Program

As Figure 1 describes, participants attending EP or physiotherapy practices allocated to the comparison group will receive a 12-week program that is more self-directed, has fewer consultation sessions, and incorporates fewer behavioral support strategies than the Active Choices program (ie, education, self-monitoring, and action planning only). The comparison program consists of two 1-hour face-to-face consultations (held in Weeks 1 and 12) that participants will complete individually with an Active Choices consultant. During the consultation in Week 1, participants will receive education about PA and identify their PA preferences. They will also be given materials to help them identify local opportunities for their PA choices and to develop their PA action plan independently at home. At the consultation in Week 12, participants will reflect on their progress during the past 12 weeks and identify their PA action plan for continuing to self-manage PA. Consultations will be guided by a resource booklet, and participants will use this booklet to self-monitor their PA across the 12-week program.

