#### Concomitant Care

Involvement in the research will not replace existing treatment plans but seek to “value-add” scaffolding for behavioral support that can benefit clients and the PA specialist. Therefore, participants in practices allocated to both programs will continue to have the option of accessing allied health treatment from their EP or physiotherapist during the 24-week study period.

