### Data Analyses

Baseline descriptive statistics will be used to summarize the demographic, physical, and lifestyle behavior characteristics of participants, and data will be checked for parametric assumptions. Intention-to-treat analyses will be conducted using linear mixed effects models. This approach will be used to account for the repeated outcome measures over time and the clustered design of the study and will provide estimates on the within-group and between-group changes in accelerometer-measured moderate intensity PA, psychological well-being, and social connectedness. Sensitivity analyses will be conducted to assess the robustness of findings, and for exploratory purposes, subgroup analyses will be performed by gender, age group, and treatment history. The results of all comparative analyses will be presented with 95% confidence intervals, and statistical significance for main effects will be assessed at the 5% level. Statistical analyses will be conducted using Stata (v15; StataCorp LLC, College Station, TX).

To analyze cost consequences, we will determine the costs of Active Choices and of normal treatment alone, inclusive of both the direct costs of implementing the intervention and the implied cost to the DVA (such as the higher or lower utilization of EP or physiotherapist services relative to group allocation). Difference-in-difference analysis will be used to determine whether Active Choices contributes to cost savings, due to a possible reduction in service utilization.

Consistent with recognized guidelines for qualitative data analyses [20], members of our research team will thematically analyze and independently review interview data and discuss the range of responses to agree on key themes. We will use this qualitative approach to triangulate our findings from the statistical analyses (eg, the impacts of the program on self-managed PA) and determine the factors that encouraged or discouraged engagement with the Active Choices program.

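### The cost analysis names normal treatment alone as comparator, but no arm receives that; the between-arm analysis estimates Active Choices versus the comparison program

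*Protocol article*

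**What the plan says.** The Data Analyses section of the protocol article describes the cost-consequence analysis in two sentences. It states the comparison as "we will determine the costs of Active Choices and of normal treatment alone". The cost components on each side are then listed, in these words: "inclusive of both the direct costs of implementing the intervention and the implied cost to the DVA". Its example of the second component is "such as the higher or lower utilization of EP or physiotherapist services relative to group allocation". It then gives the estimator: "Difference-in-difference analysis will be used to determine whether Active Choices contributes to cost savings".

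Other sections define what the arms receive:

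- Study Design and Setting: practices "will be randomly assigned to the Active Choices or comparison program, using an allocation ratio of 1:1". There are two arms and no third.
- Comparison Program: the control arm has two 1-hour face-to-face consultations, in Weeks 1 and 12, "that participants will complete individually with an Active Choices consultant". It also has education about physical activity, materials for finding local options and planning at home, and a booklet for self-monitoring.
- Concomitant Care: "participants in practices allocated to both programs will continue to have the option of accessing allied health treatment" during the 24 weeks.
- Health Service Data: service records are sought for trial participants, covering treatment before recruitment as well as the intervention and follow-up periods.

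**The concern.** The comparator named for the cost analysis is not one of the trial's arms. The control arm receives a structured program delivered by the same kind of consultant, in addition to whatever normal treatment its participants choose to use. The word *alone* therefore contradicts the article's own description of that arm.

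The wording also lets the two halves of the cost comparison refer to different comparators. Service use is to be compared by allocation, which means against the comparison program. Delivery cost is described for the intervention, in the singular, next to a comparator that has no program cost. If the two were netted on those terms, the result would answer neither question cleanly.

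At stake is how a cost-saving statement would be read. The Department of Veterans' Affairs funds the study and pays for the services, and the abstract presents the findings as pilot data for up-scaling. A reader told that the comparison is with normal treatment alone would take the result as the saving from adding Active Choices to current practice. The randomised contrast does not estimate that.

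**Working it through.** The article states no cost figure, so there is none to reproduce. The check sets the named comparator beside the design, and then does arithmetic on scheduled consultation time.

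**1. What each group receives**

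| | Program delivered | Normal treatment | Present in the trial? |
|---|---|---|---|
| Active Choices arm | Active Choices | Optional | Yes |
| Comparison arm | Comparison program | Optional | Yes |
| Normal treatment alone | None | Yes | No arm; no outside group described |

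**2. What the difference-in-difference estimates**

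Let *e_A* and *e_C* be the effects of Active Choices and of the comparison program on service cost, each relative to normal treatment alone (negative means less use). The estimator is

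(post − pre in the Active Choices arm) − (post − pre in the comparison arm).

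Under the usual assumptions it estimates *e_A − e_C*. It equals *e_A*, the effect against the named comparator, only if *e_C* = 0. If the comparison program lowers service use (*e_C* < 0), the estimated saving is smaller than the saving against normal treatment by the amount |*e_C*|. If the comparison program raises service use, the direction reverses. The article gives no value for *e_C*.

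The pre-recruitment records do not supply the missing comparator. In this estimator they are the baseline for both arms. Used alone they give a before-after figure. That figure is confounded with time, because the eligibility criteria select people whom their practitioner judges ready to move from supervised treatment to self-management, so service use might change without any program.

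**3. Scheduled consultation time per participant** (Interventions section)

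- Active Choices: 2 × 60 + 2 × 30 = 180 min
- Comparison program: 2 × 60 = 120 min
- Difference between the arms as designed: 180 − 120 = 60 min
- Difference if the control side is given no program cost: 180 − 0 = 180 min, and 180 / 60 = 3

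At the planned 26 participants per arm:

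- Active Choices: 26 × 180 / 60 = 78 h
- Comparison program: 26 × 120 / 60 = 52 h, the amount left uncosted on the narrower reading

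This covers consultation time only. Booklets, text-message reminders and other inputs are excluded. The article gives no unit costs, so no monetary figure follows.

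**4. Netting the two halves**

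Let *D_A* and *D_C* be the delivery costs. A consistent net cost is one of:

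- against the comparison program: (*D_A − D_C*) + (*e_A − e_C*)
- against normal treatment alone: *D_A + e_A*

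The mixed version, *D_A* + (*e_A − e_C*), exceeds the first by *D_C* and exceeds the second by −*e_C*. So if *D_C* is omitted and *e_C* is negative, the mixed version makes Active Choices look more costly than either consistent contrast would.

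**The case against.** The strongest reply is that this is a loose label in an exploratory analysis. Much of that stands.

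- *The analysis can be run.* A reader might infer that the planned cost comparison is impossible. It is not. The difference-in-difference by allocation is feasible and contrasts Active Choices with the comparison program. A cost of normal treatment before either program can also be described from the pre-recruitment records. What is unavailable is a randomised or concurrent contrast with normal treatment alone.
- *The comparison program is not stated to be costed at zero.* A reader might infer that its cost drops out. The article's use of *intervention* does not settle this. The comparison program is described under the Interventions heading, and the Process and Qualitative Measures section refers to the 12-week intervention for both groups, while the Active Choices Program section uses the term for the Active Choices arm. Itemised costing may also reasonably be left to a fuller document.
- *The threefold ratio is conditional.* It is an overstatement only if the comparison program goes uncosted and the target is the between-arm contrast. Against normal treatment alone, 180 minutes is the correct added consultation time.
- *A wrong conclusion for the funder is not shown.* Without unit costs or utilisation figures, the documents do not support saying that the cost-saving conclusion would be wrong. If the comparison program goes uncosted and itself lowers service use, both distortions tend to understate a saving, so a missed saving is likelier than a false one.

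The reply does not remove the mismatch. If the label is shorthand for the control arm, it contradicts the Comparison Program section and should be corrected all the same. This is a stated comparator that the design does not contain, so it is not a matter of detail deferred to an analysis plan.

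**Conclusion.** The point holds as a mislabelled comparator. The Data Analyses section sets Active Choices against normal treatment alone, but the control arm receives the comparison program plus optional normal treatment. The between-arm difference-in-difference therefore estimates Active Choices versus the comparison program, and anything said about normal treatment alone can only be descriptive.

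Two consequences are conditional. If the comparison program's delivery is not costed, the between-arm difference in scheduled consultation time is taken as 180 rather than 60 minutes per participant. If the comparison program itself reduces service use, the between-arm result understates the saving against normal treatment. The first rests on the consultation schedule in the article. The second gives a direction only, because no effect size is available.

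The weight is moderate. The article describes a proof-of-concept study that will explore effects on service use and costs, and access to the service data still depends on custodian approval. The primary outcome and the secondary outcomes are unaffected.

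**What to change.** In the Data Analyses section:

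1. Replace normal treatment alone with the comparison program plus optional normal treatment as the cost comparator.
2. State that delivery of both programs is costed.
3. Define the difference-in-difference, and every cost-saving statement drawn from it, as Active Choices versus the comparison program.
4. Label any comparison with normal treatment alone, including one built on pre-recruitment service history, as descriptive and non-randomised.

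The cost is a few sentences of wording and a log of consultant time in both arms. No additional participants or data sources are needed. The article reports that recruitment had not started, so at that stage the change could be made prospectively.

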### Sample Size

The reference parameters used to calculate the sample size were based on a recent large-scale survey conducted by our team, which examined accelerometer-measured PA in nearly 700 adults living in Brisbane, Australia. This study found participants accumulated an average of 10 minutes/day (70 minutes/week) of at least moderate intensity PA [11]. For our study, sample size was calculated based on change in accelerometer-measured PA, from baseline to 24 weeks, between the 2 groups, in order to detect a minimum average increase of 11 minutes/day (77 minutes/week) of moderate intensity PA. In addition to the PA observed in our reference study [11], this is equivalent to the minimum amount required to achieve standard Australian PA recommendations of 150 minutes/week of moderate intensity PA [12]. Assuming an average of 10 minutes/day (standard deviation of 12.7 minutes/day) at baseline, power of 80%, and significance level of 5%, our power analysis determined that a minimum sample size of 42 (21 in each group) is needed to detect a minimum average increase of 11 minutes/day in moderate intensity PA. To allow for 20% loss to follow-up and 10% noncompliance with PA device use, 52 participants will be recruited to the study (26 in each group).

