### Health Service Data

In addition to the measures that will be administered through the trial, we will also seek DVA data custodian approval to access participants’ deidentified health service data. We will use these data to assess treatment history prior to recruitment and health service utilization and costs to the DVA for providing these services during the intervention and follow-up period. This will enable us to determine the cost consequences of the program.

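### Difference-in-difference is the sole basis for the exploratory cost-savings conclusion, and in this randomised design it is usually less precise than adjusting for prior service use

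*Protocol article*

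**What the plan says.** All references are to the protocol article.

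- **Data Analyses** fixes the method for costs: "Difference-in-difference analysis will be used to determine whether Active Choices contributes to cost savings, due to a possible reduction in service utilization". The linear mixed models in the same section are stated for "between-group changes in accelerometer-measured moderate intensity PA, psychological well-being, and social connectedness"; costs and service use are not listed there.
- **Health Service Data** describes the source, subject to approval by the data custodian. On the period before the trial: "We will use these data to assess treatment history prior to recruitment". On the period after: "costs to the DVA for providing these services during the intervention and follow-up period".
- **Study Design and Setting** says practices "will be randomly assigned to the Active Choices or comparison program, using an allocation ratio of 1:1". It adds: "Randomization will be performed using a simple randomization procedure, based on a computer-generated sequence". Balancing on prior service use is not mentioned.
- **Sample Size** plans 52 participants, 26 per group.
- **Introduction** presents the cost and utilisation question as exploratory, within a proof-of-concept study.

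**The concern.** Difference-in-difference is mainly a tool for groups that were not randomised. Here allocation is random, and the prior data are at hand to serve as a covariate. Subtracting each participant's prior use sets its coefficient at 1, whereas with equal variances before and after the best linear coefficient is r. If r is below 1, the subtraction over-corrects. If Active Choices happens to draw participants with heavier prior use, their expected fall toward the mean counts as a saving. If it draws lighter users, a real saving is masked.

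At stake is the precision of the only analysis behind the cost-savings statement, in a trial of 52 participants whose practices are allocated by simple randomisation.

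**Working it through.** **Figures in the plan.** The article gives no figure for the cost analysis. Its sample size of 42 concerns physical activity and reproduces: 2 x (1.96+0.84)^2 x 12.7^2 / 11^2 = 20.9, so 21 per group. It does not bear on this point.

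**Inputs.** From the article: 26 per group, practices randomised. Assumed, because not given: r, ICC, number of practices, stability of practice effects over time, and equal pre and post SDs (set to 1).

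**Step 1: no clustering.** Variance per participant is 2(1-r) for difference-in-difference and 1-r^2 with baseline as covariate, so the ratio is 2/(1+r).

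| r | 2(1-r) | 1-r^2 | ratio |
|---|---|---|---|
| 0.3 | 1.40 | 0.91 | 1.54 |
| 0.5 | 1.00 | 0.75 | 1.33 |
| 0.7 | 0.60 | 0.51 | 1.18 |
| 0.9 | 0.20 | 0.19 | 1.05 |

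A simulation of 20,000 null trials agrees. Estimator SDs for difference-in-difference against baseline adjustment are 0.327 v 0.269, 0.278 v 0.244 and 0.214 v 0.200 at r = 0.3, 0.5 and 0.7. Both estimators average about 0. At r = 0.3 difference-in-difference is also less precise than ignoring prior use (0.327 v 0.280); above r = 0.5 it is more precise than that.

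**Step 2: shift given a chance imbalance.** With imbalance d in participants' prior use, the shift is -(1-r)d. The SD of d is sqrt(2/26) = 0.28 without clustering. For d = 0.3 the apparent saving is 0.7 x 0.3 = 0.21, 0.5 x 0.3 = 0.15 and 0.3 x 0.3 = 0.09 SD at r = 0.3, 0.5 and 0.7. Simulated slopes on d were -0.68, -0.50 and -0.29, against about 0 for baseline adjustment.

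This is Step 1 seen conditionally: 2(1-r) - (1-r^2) = (1-r)^2, which is the variance of the shift.

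**Step 3: clustering.** Let k be practices per arm, s the pre-post correlation of practice effects, r the correlation within practices, and b the fitted slope, approximately ICC x s + (1-ICC) x r.

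- Difference-in-difference: 2[2(1-s)ICC/k + 2(1-r)(1-ICC)/26]
- Baseline-adjusted: 2[(1-2bs+b^2)ICC/k + (1-2br+b^2)(1-ICC)/26]

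Three cells:

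- k=6, ICC 0.05, s=0.5, r=0.3, b=0.31: 2(0.00833+0.05115) = 0.1190 against 2(0.00655+0.03325) = 0.0796; ratio 1.49.
- k=4, ICC 0.05, s=1, r=0.5, b=0.525: 2(0.03654) = 0.0731 against 2(0.00282+0.02743) = 0.0605; ratio 1.21.
- k=2, ICC 0.10, s=1, r=0.3, b=0.37: 2(0.04846) = 0.0969 against 2(0.01985+0.03167) = 0.1030; ratio 0.94.

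These treat b as known. Simulation, which estimates b, gives somewhat lower ratios. Over 2-13 practices per arm, ICC 0.05-0.10, s 0.5-1 and r 0.3-0.7, it gives about 1.04-1.47. The exception is 2 practices per arm with ICC 0.10 and s=1, at about 0.87-0.91. The ends move by a few hundredths with simulation error and with how r is defined.

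**The case against.** The strongest case for the plan is that practices, not participants, are allocated. A lasting difference between practices, say in referral habits, does not regress to the mean. Difference-in-difference removes it, and a covariate slope below 1 leaves part of it in. With fully stable practice effects, the false effect per unit of practice-level imbalance is about 0 for difference-in-difference and about 0.7, 0.5 and 0.3 for baseline adjustment at r = 0.3, 0.5 and 0.7.

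Selection works the same way. Under Recruitment and Eligibility Criteria, the practices' own clinicians screen and refer clients. If they do so knowing their allocation, a stable difference of 0.3 SD (assumed) at r = 0.5 would bias the adjusted estimate by 0.5 x 0.3 = 0.15 SD and difference-in-difference by about 0. This stands, and it is the reason to keep difference-in-difference as a second analysis.

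Stronger readings that a reader might infer are not supported:

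- *That difference-in-difference is biased, or that false savings are a harm on top of lost precision.* It is unbiased over randomisations. The conditional shift and the extra variance are the same thing, and a valid confidence interval reflects it.
- *That 52 participants work like 34 to 44.* That follows from 2/(1+r), which ignores clustering.
- *That baseline adjustment has no downside.* The practice and selection arguments above show one.
- *That the pre and post periods are mismatched.* The article gives no look-back length, which a condensed article may leave to the full protocol, and baseline adjustment needs the same decision.

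**Conclusion.** The point holds as an improvement to an exploratory analysis, not as an error that invalidates it. Under the assumed ranges, the variance ratio of about 1.04-1.47 means a standard error about 2% to 21% larger than baseline adjustment would give (square roots 1.02 and 1.21). Without clustering the ratio would be 1.18-1.54 for the same r. If r is near 0.9 the loss is small.

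The advantage reverses only in the corner of about 2 practices per arm, ICC near 0.10 and fully stable practice effects. The article does not give the number of practices, so that corner cannot be excluded. The result also assumes that imbalance in prior use arises by chance rather than by selective recruitment.

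**What to change.** In Data Analyses, make the main cost and service-use analysis a between-arm comparison of the measure over the intervention and follow-up period. Adjust it for the same measure before recruitment and account for clustering by practice, for example within the linear mixed model framework already planned for the other outcomes. Keep difference-in-difference as a sensitivity analysis and report both.

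The cost is a wording change and about one degree of freedom. It needs no new participants and no data beyond those already being requested. Baseline adjustment does not fully remove stable practice differences or selective recruitment. The retained difference-in-difference result covers that, and a clear disagreement between the two would be a reason to examine prior use by practice.
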